| RBC | Red blood cell count |
| Hb | Hemoglobin |
| PLT | Platelet count |
| TBIL | Total bilirubin |
| DBIL | Direct bilirubin |
| ALT | Alanine aminotransferase |
| AST | Aspartate aminotransferase |
| AKP | Alkaline phosphatase |
| TP | Total protein |
| ALB | Albumin |
| BUN | Urea/urea nitrogen |
| Cr | Creatinine |
| Ccr | Endogenous creatinine clearance rate |
| GLU | Fasting blood glucose |
| K | Potassium |
| Na | Sodium |
| Cl | Chlorine |
| Ca | Calcium |
| P | Phosphorus |
| CK | Creatine Kinase |
| CK-MB | Creatine Kinase-MB |
| cTnT | Troponin |
| INR | International Normalized Ratio |
| APTT | Activated Partial Thromboplastin Time |
| PT | Prothrombin Time |
| FIB | Fibrinogen |
| ULN | Upper limit of normal |
| SDV | Source Data Verification |
| FAS | Full Analysis Set |
| PPS | Per-protocol set |
| SS | Safety analysis set |

Protocol synopsis

| Study Drug | Irinotecan Liposomes |
| --- | --- |
| Protocol Title | A Phase I, Open-Label Clinical Study of Irinotecan Liposomes Combined with Epirubicin in Recurrent Non-Muscle Invasive Bladder Urothelium Carcinoma after Anthracyclines Treatment |
| Protocol ID | 2024-549-02 |
| Version Number | 1.0 |
| Version Date | December 17, 2024 |
| Sponsor | The First Affiliated Hospital of Chongqing Medical University |
| Study Design | A Prospective, single-center, single-arm Phase I clinical study |
| Study Nature | An investigator-initiated clinical study |
| Study Population | Patients with recurrence of bladder urothelial carcinoma after anthracycline treatment |
| Sample Size | An estimated 6-9 participants will be recruited per arm, yielding a total target enrollment of 12-18 participants across both arms. |
| Objective | 1. To explore the safety profile (including dose-limiting toxicity), efficacy, and tolerability of neoadjuvant Irinotecan liposome combined with Epirubicin in non-muscle invasive bladder cancer (NMIBC) patients with anthracycline-resistant recurrent disease. 2. To explore the epigenetic mechanism by which Irinotecan liposome target and inhibit DNA homologous recombination repair to reverse anthracycline chemotherapy resistance in bladder cancer |
| Endpoints | 1. Primary Endpoints:  Incidence and frequency of Dose-Limiting Toxicity (DLT)  2. Secondary Endpoints:  (1) Adverse drug reactions;  (2) Recurrence-Free Survival (RFS);  (3) Disease Control Rate (DCR);  3. Tumor Response Evaluation (per RECIST 1.1 criteria):   - Complete Response (CR): Disappearance of all target lesions; no new lesions. - Partial Response (PR): ≥30% decrease in the sum of diameters of target lesions. - Stable Disease (SD): Neither sufficient shrinkage to qualify for PR nor sufficient increase to qualify for PD. - Progressive Disease (PD): ≥20% increase in the sum of diameters of target lesions or appearance of new lesions. |
| Study Procedures | 1. Arm A: TURBT unresectable  If the recurrent tumor can't be excised by TURBT, participants will be assigned to this arm. Participants in this arm will complete the neoadjuvant therapy with Irinotecan liposome (intravenous injection, once every two weeks for 1 month, dose increasing regimen: 37.6 mg/m^2^ and 56.5mg/m^2^) and Epirubicin (intravesical instillation, once a week for 1 month, 50 mg), and the therapeutic effect was evaluated by pelvic enhanced MRI and cystoscopy. Judged by two senior urologists, patients with complete response and partial response were treated with TURBT and intravesical therapy. Patients with stable disease or progressive disease received subsequent therapy at the investigator's discretion. Participants will visit the clinic once every 2 weeks for checkups and tests.  2. Arm B: TURBT resectable  If the recurrent tumor can be excised by TURBT, participants will be assigned to this arm (Arm B). Participants in this arm will complete TURBT with immediate intravesical instillation of Epirubicin (50 mg) within 24 hours after surgery. During the induction phase (the first 1 month after surgery), participants will receive the combined therapy with irinotecan liposome (intravenous injection, once every two weeks for 1 month, dose increasing regimen: 37.6 mg/m^2^ and 56.5mg/m^2^) and Epirubicin (intravesical instillation, once a week for 1 month, 50 mg). In the next 6 months, participants will continue the intravesical instillation treatment with Epirubicin (once a month, 50 mg). Participants will visit the clinic once every 2 weeks for checkups and tests in the first month, and once every 3 months after the first month. |
| Inclusion Criteria | Subjects can participate in the study only if all the following criteria are met:   1. Patients with cTa-cT1N0M0 non-muscle invasive bladder cancer (NMIBC); 2. Disease recurrence following intravesical anthracycline-based chemotherapy; 3. Recurrent tumors confirmed as cTa-cT1N0M0 bladder urothelial carcinoma; 4. No prior systemic chemotherapy exposure; 5. Measurable lesions per Response Evaluation Criteria in Solid Tumors (RECIST); 6. Eastern Cooperative Oncology Group (ECOG) performance status 0-1. |
| Exclusion Criteria | Subjects who meet any of the following criteria are not eligible to enter the study:   - 1. Age <18 years;   2. Subjects with severe cardiac, cerebral, hepatic, or renal dysfunction;   3. Subjects with severe malnutrition;   4. Subjects with psychiatric disorders or those lacking insight/unable to provide accurate expression;   5. Concurrent malignancies in other organs;   6. Presence of systemic infectious diseases. |
| Discontinuation Criteria | Discontinuation of study treatment does not equate to study withdrawal. Participants who discontinue study treatment must continue to complete all remaining study visits as required by the protocol. Study treatment must be discontinued if a participant meets any of the following criteria:  1. The study participant withdraws informed consent and refuses to continue receiving the investigational drug treatment;  2. The investigator determines that the participant's clinical symptoms have worsened/performance status has deteriorated;  3. Disease progression is confirmed per RECIST v1.1 criteria;  4. Despite dose modification, the participant remains unable to tolerate adverse events, including any clinical AEs, laboratory abnormalities, or other medical conditions;  5. The participant commits a major protocol violation or demonstrates non-compliance with medical instructions;  6. Occurrence of pregnancy, loss to follow-up, or death of the participant;  7. Other circumstances where the investigator deems it necessary to discontinue the investigational drug treatment. |
| Withdrawal Criteria | Reasons for Study Withdrawal:  1. Withdrawal of informed consent - Participant refuses further study participation and follow-up.  2. Lost to follow-up  3. Death of participant  4. Study termination  5. Other investigator-determined reasons for withdrawal |
| Termination Criteria | The study may be prematurely terminated or temporarily suspended based on the following criteria:  1. Identification of unexpected, significant, or unacceptable risks to study participants  2. Discovery of critical protocol flaws during trial execution |
| Safety | Any adverse events (AEs) that occurred in all subjects during the clinical study period will be observed, including abnormal clinical symptoms and vital signs, and abnormalities in laboratory tests. The clinical characteristics, severity, time of occurrence, duration, treatment methods, and prognosis of adverse events will be recorded; meanwhile, the correlation between adverse events and the study drugs will be determined. The safety of drugs is evaluated according to National Cancer Institute's Common Terminology Criteria for Adverse Events (NCI-CTC AE) version 5.0. |
| Statistical Analysis | For the primary endpoint, the DLT Analysis Set (DAS) included all participants who were in the DLT evaluation period and either completed the DLT assessment or experienced a DLT during the evaluation period. This analysis set will be used for the analysis and summary of DLT events.  For Secondary Endpoints, such as RFS, the median value and 95% CI are estimated and survival curves are obtained using the Kaplan-Meier method. The log-rank test is used to compare the survival between the two groups. DCR with 95% CI are calculated, and comparisons between treatment groups are performed using a Cochran-Mantel-Haenszel (CMH) test or chi-square test. Two independent samples will be compared for the differences between the two groups in QoL scores by the t-test or Wilcoxon rank sum test. |
| Study Schedule | Enrollment date of the first subject: January 2025  Estimated date of the primary completion date: April 2025  Estimated date of the end of the study: December 2025 |

1. Background

## 1.1 Overview of Bladder Cancer

Bladder cancer has emerged as one of the most common genitourinary malignancies in China, currently ranking as the eighth most frequently diagnosed cancer among Chinese male populations. With its characteristically high incidence, frequent recurrence patterns, and substantial mortality burden, this disease represents a major public health challenge in contemporary China [1]. Among histological subtypes, non-muscle invasive bladder cancer (NMIBC) constitutes approximately 75% of incident cases at initial diagnosis, representing the predominant clinical presentation. This form demonstrates particularly aggressive recurrence patterns, with published 5-year recurrence rates ranging from 31% to 78% across various clinical series [2]. The substantial recurrence risk, coupled with potential progression to muscle-invasive disease, underscores the critical need for effective therapeutic interventions. To mitigate recurrence and disease progression, adjuvant intravesical instillation therapy following transurethral resection of bladder tumor (TURBT) has been established as the standard treatment regimen for NMIBC.

## 1.2 Therapeutic Challenges in NMIBC

The standard care for NMIBC involves Transurethral resection (TURBT) followed by adjuvant intravesical therapy. Among chemotherapeutic options, anthracycline-based chemotherapeutic agents, particularly Epirubicin, have emerged as a first-line intravesical chemotherapy drugs for bladder cancer due to their potent antitumor activity and favorable safety profile. These agents are also widely used in treating other malignancies such as breast cancer and gastric cancer [3]. The mechanism is to inhibit topoisomerase II activity, thereby blocking DNA replication and transcription to suppress tumor cell proliferation. In addition, Epirubicin can intercalate between DNA base pairs, inducing DNA double-strand breaks and promoting tumor cell apoptosis [4]. Although bladder cancer cells demonstrate initial sensitivity to first-line chemotherapeutic agents like Epirubicin, the majority of patients develop varying degrees of acquired resistance within several years, resulting in elevated postoperative recurrence rates, increased tumor aggressiveness upon recurrence and the greater technical difficulty in surgical resection of recurrent lesions. Therefore, addressing this acquired chemoresistance represents a critical therapeutic challenge in NMIBC management.

Tumor heterogeneity represents one of the greatest challenges in contemporary cancer therapeutics. Emerging evidence from multiple studies has demonstrated that epigenetic alterations in tumors serve as a pivotal mechanism underlying therapy resistance and poor clinical outcomes in cancer patients [5-7]. Under drug selection pressure, tumor cells adapt to their microenvironment through a fundamental remodeling process spanning multiple molecular levels---including DNA, RNA, and protein networks. For instance, tumor subclones harboring specific driver mutations may acquire selective advantages over neighboring cells, ultimately driving clonal evolution and conferring therapeutic resistance. Multiple post-hoc analyses of tissue specimens from prior bladder cancer chemotherapy trials have demonstrated that mutations in DNA damage repair (DDR) pathway genes and other molecular markers exhibit predictive value for treatment efficacy in muscle-invasive bladder cancer (MIBC) [8-10].

Interestingly, in the bladder cancer cohort treated with Epirubicin infusion chemotherapy initiated by the collaborating unit, we conducted multi-omics testing on tissue specimens before and after treatment. Whole-exome sequencing results showed that the mutation rate of DDR-related genes was significantly increased in the tumor tissues of drug-resistant patients. Further modification omics analysis suggested that the lactylation modification levels of several key enzymes for DNA homologous recombination repair, such as BLM, RAD51, and MER11, were significantly up-regulated in drug-resistant patient tumor cells. Transcriptome sequencing analysis found that differentially expressed genes between tumors of patients without recurrence within 1 year and those of recurrent patients were enriched in multiple DDR-related signaling pathways such as homologous recombination repair and DNA metabolism. We further conducted a retrospective analysis of NMIBC patients resistant to anthracycline chemotherapy, and found that activation of homologous recombination repair also indicated anthracycline resistance. Then, clinically, can the reversal of Epirubicin chemotherapy resistance be achieved by inhibiting the homologous recombination repair pathway in these patients?

In our preliminary experiments, we observed significantly elevated levels of lactylation modification on BLM, a crucial helicase involved in DNA homologous recombination repair, in both EPI-resistant bladder cancer tissues and in vitro induced EPI-resistant bladder cancer cell lines. Inhibition of lactylation modification at the K24 site of BLM effectively reversed EPI resistance. Through molecular docking and high-throughput small molecule screening, we identified that irinotecan can bind to the BLM-K24 drug-binding pocket, thereby reducing BLM lactylation and enhancing EPI chemosensitivity. Further validation using EPI-resistant bladder cancer and breast cancer PDX models and organoid models demonstrated that the combination of irinotecan and EPI successfully reversed EPI resistance without inducing additional drug toxicity in mouse models.

## 1.3 Irinotecan Liposome

Irinotecan is a semi-synthetic derivative of camptothecin that specifically binds to topoisomerase I, inducing reversible single-strand breaks and consequently unwinding the DNA double-helix structure. Both irinotecan hydrochloride and its active metabolite SN-38 can bind to the topoisomerase I-DNA complex, thereby preventing the religation of the broken single strands [11, 12]. Recent structure-activity relationship studies have demonstrated that the lactone ring in the structure of camptothecin drugs such as irinotecan is an essential group for antitumor activity. However, under physiological conditions, it rapidly hydrolyzes into an inactive open-ring form, thereby limiting the antitumor efficacy [13, 14]. In contrast, liposome-based microvesicular drug delivery systems offer unique advantages, including enhanced drug solubility, controlled release properties, improved stability, and superior tumor-targeting capabilities. These features are of significant importance in potentiating the antitumor effects, reducing toxicity, and improving the bioavailability of chemotherapeutic agents [15, 16]. Irinotecan hydrochloride liposomal injection is a novel formulation developed by modifying the existing marketed irinotecan hydrochloride injection and its lyophilized powder. This reformulation enables passive tumor targeting, protecting irinotecan from premature conversion to its active metabolite, SN-38. Consequently, it prolongs the drug’s circulation time, enhances its accumulation and retention within tumor tissues, and strengthens its tumor growth inhibitory effects. This mechanism of action has been evaluated and validated in clinical studies. The global multicenter, randomized controlled phase III NAPOLI-1 trial published in The Lancet and its Asian subgroup analysis reported in Cancer Science demonstrated that for metastatic pancreatic cancer patients who failed prior gemcitabine-based chemotherapy, liposomal irinotecan combined with 5-FU/LV significantly improved overall survival (OS) with manageable toxicity, showing particularly enhanced survival benefits in the Asian population [13, 15, 16]. These preclinical findings suggest liposomal irinotecan may emerge as a key intervention for overcoming chemotherapy resistance in bladder cancer by inhibiting homologous recombination repair.

Building upon this scientific foundation and preliminary research findings, the current project proposes to conduct a prospective single-arm Phase I clinical study investigating combination therapy with Irinotecan Liposome and Epirubicin for NMIBC patients with anthracycline-resistant recurrent disease. This study is expected to provide a novel, highly effective and low-toxicity therapeutic option for reducing post-anthracycline chemotherapy recurrence and improving treatment outcomes in recurrent tumors, thereby offering a new precision medicine approach for bladder cancer.

# 2. Study Objective and Anticipated Outcomes

## 2.1 Study Objective

(1) To explore the safety profile (including dose-limiting toxicity (DLT)), efficacy, and tolerability of neoadjuvant liposomal irinotecan combined with Epirubicin in NMIBC patients with anthracycline-resistant recurrent disease.

(2) Building upon prior clinical and mechanistic investigations, this study aims to elucidate the epigenetic mechanisms by which liposomal irinotecan reverses anthracycline chemotherapy resistance in bladder cancer through targeted inhibition of DNA homologous recombination repair.

## 2.2 Anticipated Outcomes

(1) Establish DLT and characterize the safety profile, tolerability, and antitumor efficacy of this combination regimen.

(2) Publish research findings in a peer-reviewed journal with an impact factor >5.

(3) Secure provincial/ministerial-level research funding (1 grant application).

(4) Train 2-3 graduate students to clinical/translational research competency.

# 3. Study Endpoints

## 3.1 Primary Endpoints

Incidence and frequency of DLT

## 3.2 Secondary Endpoints

(1) Adverse drug reactions: Any noxious, unintended response to the investigational drug(s) (Irinotecan liposome + Epirubicin) at any dose, causally related to treatment (per WHO-UMC causality assessment criteria).

(2) Recurrence-Free Survival (RFS): Time from treatment initiation to histologically confirmed tumor recurrence, radiologic progression or death from any cause.

(3) Disease Control Rate (DCR): Proportion of patients achieving complete response (CR), partial response (PR) and stable disease (SD).

Note: Tumor Response Evaluation (per RECIST 1.1 criteria):

- CR: Disappearance of all target lesions; no new lesions.
- PR: ≥30% decrease in the sum of diameters of target lesions.
- SD: Neither sufficient shrinkage to qualify for PR nor sufficient increase to qualify for progressive disease (PD).
- PD: ≥20% increase in the sum of diameters of target lesions or appearance of new lesions.

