## 4.2 Dose Escalation Regimen

The dose-escalation scheme is designed based on a comprehensive evaluation of non-clinical in vitro pharmacodynamic data, existing clinical efficacy evidence and Safety profiles.

Arm A: Participants in this arm will complete the neoadjuvant therapy with irinotecan liposome (intravenous injection, once every two weeks for 1 month, dose increasing regimen: 37.6 mg/m2 and 56.5mg/m2) and epirubicin (intravesical instillation, once a week for 1 month, 50 mg).

Arm B: In the induction phase, the first three participants received a reduced dose of irinotecan liposomes (37.6 mg/m2, once every two weeks) in combination with standard intravesical EPI chemotherapy (50 mg, once a week) during the first cycle. If the combination was well tolerated, the irinotecan liposome dose was escalated to the full dose (56.5 mg/m2, once every two weeks) in the second cycle. The remaining three participants received the full dose of irinotecan liposomes (56.5 mg/m2, once every two weeks) along with standard EPI (50 mg, once a week) in both treatment cycles. Epirubicin was given at a fixed dose of 50 mg q1w for 4 cycles. In the maintenance phase, Epirubicin 50 mg q1m was intravesical instillation for a total of six cycles.

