# 8. Overview of drugs

**Irinotecan Hydrochloride Liposome Injection:**

Specification: 8ml: 37.66mg (as C₃₃H₃₈N₄O₆)

Manufacturer: Jiangsu Hengrui Pharmaceuticals Co., Ltd.

Dosage Form: Injection

Route of Administration: Intravenous infusion

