## 12.4 Safety Follow-up

The follow-up shall be conducted at 7 days (±2 days) after the last dose of study medication and includes the following:

- Adverse event assessment;
- Documentation of concomitant medications and concomitant therapies;
- Recording of subsequent anti-tumor therapies.

Collection of adverse events begins from the signing of the ICF and continues until the end of the safety follow-up period (i.e., 7 days after the last administration of the study drug or upon screening failure).If a study participant initiates new anti-tumor therapy before the end of the safety follow-up period, only AEs/SAEs suspected to be related to the study drug will be collected from the start of the new anti-tumor therapy until the end of the safety follow-up period. Any death occurring during the safety follow-up period must be reported as an SAE, regardless of whether the participant received other treatments.

After the safety follow-up period, only SAEs considered to be related to the investigational drug will be collected. For participants following the last dose of Irinotecan liposome, clinical follow-up or telephone visits will be conducted to collect information on survival status, AEs, concomitant medications, and concomitant therapies. Investigators may schedule additional visits as needed to follow up on the resolution of AEs.

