## 14.5 SAE Reporting Procedure

Upon occurrence of an SAE, whether for initial reporting or follow-up reporting, the investigator must immediately complete, sign, and date a Serious Adverse Event/Adverse Event Report Form of special Interest and report it to the appropriate authorities

All SAEs should be recorded in detail, including symptoms, severity (according to CTCAE 5.0), correlation with each study drug, occurrence time, treatment time, measures taken for each study drug due to SAEs, follow-up time and methods, and outcome. If an SAE is considered by the investigator to be unrelated to the study drug but potentially related to study conditions (e.g., discontinuation of the original treatment, or coexisting conditions during the course of the trial), this relationship should be detailed in the narrative section of the SAE report form. If the intensity of an ongoing SAE or its relationship to the study drug changes, a follow-up report should be submitted immediately. If investigators believed that the previously reported SAEs were misreported, they could provide corrections, retractions, or de-escalation instructions in the follow-up report and report them according to SAE reporting procedures.

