## 15.5 Statistical Analysis

### 15.5.1 Analysis datasets

(1) Full Analysis Set (FAS):

The Full Analysis Set (FAS) consists of all study participants who signed the ICF, were enrolled in the study, and received at least one dose of the investigational drug. The FAS serves as the primary analysis set for efficacy endpoints in this study. For cases where the full treatment course was not observed, the last observation carried forward (LOCF) method will be applied to impute missing data for the final analysis.

(2) Per-protocol set (PPS):

PPS will be defined as all subjects who met the trial protocol, did not take prohibited drugs, with favorable compliance, and completed CRF. No imputation of missing data. Efficacy analysis was conducted based on PPS populations.

(3) Safety analysis set (SS):

The SS population will serve as the population for the safety analysis. All randomized subjects have received at least one dose of the research drug and have a post-administration safety record.

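### The study drug is irinotecan liposome alone in some sections and irinotecan liposome plus epirubicin in others, so the Arm B adverse-event window has no fixed end and may miss epirubicin maintenance

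*Protocol*

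**What the plan says.** **Irinotecan liposome alone.** The first row of the synopsis reads "Study Drug | Irinotecan Liposomes". Section 8, the overview of drugs, has one entry, "Irinotecan Hydrochloride Liposome Injection", and none for epirubicin.

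**Both drugs.** Section 3.2 defines the adverse-drug-reaction endpoint as "Any noxious, unintended response to the investigational drug(s) (Irinotecan liposome + Epirubicin) at any dose, causally related to treatment". Section 14.5 asks investigators to record "measures taken for each study drug due to SAEs".

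**Undefined.** The rules that depend on the term do not say which product they mean:
- Section 12.4 ends adverse-event collection 7 days after the last administration of the study drug, then restricts collection to serious events related to the investigational drug.
- Section 14.3.1 ends it 30 days after the last administration of the investigational product.
- Section 15.5.1 admits to the full analysis set (FAS) those who "were enrolled in the study, and received at least one dose of the investigational drug". Its safety set uses yet another term, the research drug.

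Section 12.4 also contains a sentence tied to one product: "For participants following the last dose of Irinotecan liposome, clinical follow-up or telephone visits will be conducted to collect information on survival status, AEs".

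**Arm B schedule.** Epirubicin is instilled within 24 hours of TURBT, before the induction phase (section 4.1). Irinotecan liposome is given every two weeks for one month (synopsis) and epirubicin weekly, four times (section 4.2). Then: "In the maintenance phase, Epirubicin 50 mg q1m was intravesical instillation for a total of six cycles".

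**The concern.** Section 3.2 puts reactions to epirubicin inside a secondary endpoint. Whether they are collected in Arm B depends on which drug's last dose starts the closing clock, and the Protocol supports two answers. If it is irinotecan liposome, routine collection ends before most or all of epirubicin maintenance, and non-serious reactions in that phase could go unrecorded. The Arm B reaction rate would then be too low.

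This is separate from the conflict between 7 and 30 days. Settling the number of days does not say which drug starts the count. Nor can a later statistical analysis plan repair it: such a plan can define analysis sets, but it cannot recover events that were never collected.

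The same undefined term decides whether an Arm B participant who has the immediate epirubicin instillation, but never receives irinotecan liposome, belongs to the FAS and the safety set.

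**Working it through.** The Protocol states no closing date, so there is no figure to reproduce. Its only related total adds up: 2 × 6 = 12 and 2 × 9 = 18 (section 5).

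**Inputs from the Protocol**
- Irinotecan liposome in Arm B: every two weeks for one month, nominally two doses 14 days apart (synopsis).
- Window: 7 days (12.4) or 30 days (14.3.1) after the last dose.
- Epirubicin in Arm B: 1 immediate + 4 weekly + 6 monthly = 11 instillations (4.1, 4.2).
- Maintenance: months 1–6 after TURBT (4.1), or the six months after the first month, so up to month 7 (synopsis).

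**Assumptions**
- TURBT is day 0 and a month is 30.4 days.
- The first irinotecan liposome dose falls on day 1 to day 7, and weekly epirubicin starts on the same day.

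**Formula:** closing day = day of last study-drug dose + window.

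| Reading | Last dose | + 7 days | + 30 days |
| --- | --- | --- | --- |
| Irinotecan liposome only, undelayed | day 1 + 14 = 15 to 7 + 14 = 21 | day 22–28 | day 45–51 |
| Irinotecan liposome only, last dose 14 days later | day 29–35 | day 36–42 | day 59–65 |
| Epirubicin counts, last dose month 6 | 6 × 30.4 = 182.4 | day 189 | day 212 |
| Epirubicin counts, last dose month 7 | 7 × 30.4 = 212.8 | day 220 | day 243 |

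The second row covers the two-week delay that section 4.3 allows after a DLT.

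**Gap between the readings** under the same window, for a last irinotecan liposome dose on day 15: 182.4 − 15 ≈ 167 days, to 212.8 − 15 ≈ 198 days. That is essentially the whole maintenance phase.

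**Instillations outside the window, undelayed course**
- 7-day rule (day 22–28): the first maintenance instillation is at about day 30 (4.1) or day 61 (synopsis), so all 6 are outside. The fourth weekly instillation falls on the closing day itself (1 + 21 = 22; 7 + 21 = 28) and is counted as inside.
- 30-day rule (day 45–51): on the section 4.1 timing only the day-30 instillation is inside, leaving 5 outside. On the synopsis timing all 6 are outside.
- Result: 5/11 = 45% or 6/11 = 55%.

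**Analysis sets.** One participant who receives epirubicin but no irinotecan liposome is 1/9 = 11% to 1/6 = 17% of an arm of 6–9.

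**The case against.** The strongest reply is that the Protocol largely answers the question. Section 3.2 names both drugs, 14.5 speaks of each study drug, and sections 9 and 11 use the plural. Nothing says epirubicin is not a study drug. The synopsis row is a label and section 8 a product description; neither sets a clock.

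Several passages also point to recording beyond the last irinotecan liposome dose:
- The synopsis safety row covers any adverse event during the clinical study period.
- Section 4.1 follows adverse reactions from induction onward and names no stop.
- Section 13.2 grades and records events during the study and follow-up.
- Section 14.3.2 has investigators ask about events at every scheduled visit, and the synopsis schedules Arm B visits every three months after the first.

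This has weight. A reader might infer that maintenance reactions will certainly be lost; given these passages, the Protocol does not support that. A reader might also take the irinotecan-specific sentence in 12.4 as proof that the window closes on that drug. It is not: the sentence adds contacts at which adverse events are asked about, and its narrower term could equally suggest that study drug is the wider one.

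The objection does not remove the conflict. The sentence in 12.4 just before those added contacts limits later collection to related serious events, and 12.4 and 14.3.1 are the sections that set the closing date. A site following them, with the synopsis definition, would have grounds to stop early.

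**Conclusion.** The point stands as an unresolved contradiction that could cause under-collection, and it should be corrected. For an undelayed Arm B course, the irinotecan-only reading closes routine collection at about day 22–28 or day 45–51, against about day 189–243 when epirubicin counts. It leaves 5 or 6 of 11 planned epirubicin instillations outside the window. These figures rest on two irinotecan liposome doses 14 days apart, starting on day 1 to 7 after TURBT. A later last dose moves the irinotecan-only closing day to 36–65, still far short of day 189.

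Three limits apply:
- The number of participants with an unrecorded reaction cannot be derived, because the Protocol gives no reaction rate per instillation.
- A reader might infer that FAS membership does change. It changes only if someone receives epirubicin and no irinotecan liposome, which is possible but not shown.
- The primary endpoint is not shown to be affected: DLT has its own analysis set (15.5.3), and escalation rests on first-cycle observation (4.3).

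**What to change.** 1. Define study drug/investigational product once, as irinotecan liposome plus protocol epirubicin, in line with section 3.2. Reconcile the synopsis Study Drug row and sections 3.2, 8, 12.4, 14.3.1, 14.5 and 15.5.1 with that definition.
2. State in 12.4 and 14.3.1 that the adverse-event window runs from the last protocol dose of either drug. In 12.4, reconcile the restriction to related serious events with the sentence on later contacts that collect adverse events.
3. Report Arm B reactions separately for induction and maintenance, so that reactions to the combination are not mixed with those arising on epirubicin alone.
4. Keep everyone who received either drug in the safety set. Any requirement for an irinotecan liposome dose should apply only to the efficacy set for the combination; in the safety set it would drop epirubicin-exposed participants whose reactions section 3.2 puts in scope.

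The cost is Protocol wording and a few more months of adverse-event recording in Arm B, at instillation visits that already take place. No dose or schedule changes.
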